### Sample size

Given that our primary outcome measure is a proportion i.e. the proportion of refugee patients’ records that show a refugee health assessment was billed when it was indicated, then to detect a post-intervention increase in percentage by 25–30% (a medium-large effect) we need approximately 12 clinics per region. In each of the 12 clinics we require cross-sectional data from 30 refugee background patients at each timepoint. Sample size calculations were done using Stata statistical software stepped-wedge for clusters defined at the level of the practice, intra-class correlation coefficient of 0.05, 80% power, an alpha of 0.05 and data collected at two time points [34].

### Recruitment

The project will be promoted to general practice clinics through the partner organisations, including practice visits, newsletters and promotion through each region’s PHN website. Practices will be invited to express interest through contacting the research team. Practices will be recruited by personal contact from the study’s research officers during an on-site visit to practices that express interest. The visit will allow an opportunity to further explain the project and to obtain written informed consent. Once the practice gives informed consent, clinical staff will be approached directly (generally through a practice meeting) and asked to provide written informed consent for the practice to participate in the intervention.

Practices will be offered a $2000 honoraria in recognition of the time required by staff to participate in the study. Participating general practitioners, practice nurses and practice managers will be eligible for continuing professional development points through their respective peak and professional bodies.

### Assignment of interventions

#### Allocation

Following recruitment into the study, practices will undergo blinded, stratified random allocation into either an early or late intervention group using a minimization procedure. Early group practices will start receiving the intervention immediately after recruitment. Late group practices will start the intervention 6-months after the date of completing the initial baseline data collection to act as control for the group receiving the intervention first. To ensure that early and late study groups are similar, practices will be stratified based on region and practice size as determined by the number of full time equivalent (FTE) general practitioners (≤ 5 FTEs, > 5 FTEs). The randomization codes were generated using Minim randomization software [35]. Wherever possible, batches of two or more practices will randomised at the same time.

#### Blinding

A statistician external to the project will perform the randomisation but will be blinded to the name or location of the practice. Practices will be informed of their allocation as blinding of practices to early or late intervention will not be possible.

### Data collection methods

Evaluation of the impact of the intervention will be assessed at the level of the practice. The researchers will collect data from early intervention practices at three-time points: at baseline (prior to the start of the intervention), at 6-months (immediately after completion of the intervention), and at 12 months (6-months after the intervention has been completed). Data collection in the late intervention practices will follow the same schedule, however they will have an additional point of data collection immediately prior to the start of the intervention. Table 4 provides an overview of the data collection methods used at each time point.

**Table 4 Tab4:** Data Collection Timeline

	Practice Description Survey	Refugee Health Survey	Provider Survey	PENCS CAT4™ extract
Pre-intervention (Baseline)	x^a^	x	x	x
Post-intervention	–	x	x	x
6-months post intervention	–	–	–	x

^a^Late intervention group had two sets of baseline data collected; once at the initial recruitment and the other just before intervention began

A qualitative study is embedded within the quasi-experimental randomised controlled trial. We will use qualitative methods to generate an in-depth understanding of practice facilitation as the mechanism of change, and the key contextual determinants of change. Qualitative data will illuminate our understanding of variations in quantitative practice performance data in relation to refugee identification, interpreter use, conduct of comprehensive health assessments and referral, in response to the intervention.

The following instruments will be used to collect data:Quantitative measures**De-identified data extraction**: The PENCS CAT4**™** tool, is widely used by practices and Primary Health Networks to monitor practice performance and inform routine quality improvement interventions. The research team designed an add-on software report within the CAT4**™** tool to allow measurement of general practice performance in key refugee health quality domains including refugee identification, interpreter use and health/mental health assessments. Searches of each participating practice’s electronic clinical and practice management software will first filter all patient records where identifiers of country of birth, ethnicity or language spoken that are relevant to refugee populations have been recorded in a coded field or as free text in the patient record. All identifiable information including patient name, address, contact details will be automatically removed prior to the output being made available to the researchers. This output will be a de-identified line listed excel spreadsheet that includes (where available) residential postcode, age, gender, country of birth, ethnicity, language spoken, year of arrival, interpreter needed, list of diagnoses, date of first visit, dates of visits in the last 12 months, dates of visits where an interpreter was used, date of last health assessment and date of last mental health care plan. This data extract will be carried out at baseline and repeated at the end of the intervention period as well as at 6-months post intervention completion. Analysis will allow us to identify track changes in practice performance as a result of the quality improvement intervention.A **Practice Description survey** (Additional file 2) will be administered to the practice team at baseline and will contain questions regarding a practice’s staffing, patient load and demographics, organisational structure/governance, appointment setting systems, clinical record management systems, payment systems and processes for client transition including transfer of information. Survey items were primarily derived from the Preventive Evidence into Practice study (PEP) [33] and the Canadian Community-Based Primary Health Care Common Indicator Project [36].**A Practitioner survey** (Additional file 3) will be administered to each consenting general practitioner. This will contain questions ascertaining practice staff’s background, experience and interest in refugee health care delivery, and experience of and attitude towards using interpreters in clinical care. Survey items were derived from the Comparison of Models of Primary Care in Ontario study [37]; PEP [33]; the Community-Based Primary Health Care Common Indicator Project [36]; and the Patient-Centered Medical Home Scale [38]. The survey will be repeated at the end of the intervention period.**A Refugee healthcare survey** (Additional file 4) will be administered to each practice and their staff participating in the project by the Research Officer during the first facilitation visit to document whole-of-practice approaches to refugee care. The survey items were designed specifically for this project, informed by the areas of focus emerging from the deliberative forum. The data generated by using this tool will also inform tailoring of the practice facilitation intervention. The survey will be repeated at the end of the intervention period.b)Qualitative data**Semi-structured interviews**: Following the intervention period, we will interview Practice Facilitators (*n* = 3), research officers (n = 3) and practice staff who played a key role in intervention from two practices in each round within each region (*n* = 12 practices) to explore their experiences of being involved in the intervention. The aims of the interviews are to identify key factors affecting the fidelity, effectiveness and sustainability of the intervention.**Facilitator diary:** Practice Facilitators will maintain a reflective diary of their contacts with practices to document activities undertaken, resources provided, challenges encountered and how these were overcome.**Action plans***:* As part of the intervention, Practice Facilitators will work alongside key practice personnel to document practice goals and relevant activities relating to refugee identification, interpreter use, conduct of comprehensive health assessments and referral. Action plans will be used to monitor progress towards practice goals and (where applicable) the documentary evidence of achieving these goals.**Facilitator meeting minutes***:* The research team will maintain detailed minutes from the research officers’ meeting and the Practice Facilitator meetings.**Reports of regional needs assessments***:* Will provide additional information on the region, including refugee population demographics, distribution general practice clinics and refugee health services within the catchment and socio-political factors affecting service provision.

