Each RPT worked to characterise each region’s policy, program and service context with particular reference to the care of refugee populations. We focused specifically on barriers and enablers affecting access, transition and quality of primary care within the region. To further understand regional partnership needs, each RPT performed a focused scientific and grey literature review, analysed secondary data extracted from the Australian Bureau of Statistics Census, Department of Home Affairs Settlement Reporting Facility, settlement agencies, public health services and local councils, and conducted a series of key informant interviews with health service managers, policy advisors and clinicians. The three RPTs then met in a deliberative forum [28] to determine priority interventions, from which four core areas of activity were chosen;Physical and mental health assessments: GPs and practice nurses will have relevant skills and knowledge to conduct comprehensive refugee physical and mental health assessments.Refugee identification: general practice clinics will have accurate and accessible mechanisms in place to record and retrieve refugee identification, status, country of birth or ethnicity, year of arrival, and need for interpreter.Use of interpreters: practices will have a practice protocol for using interpreters, and ensure that staff have appropriate knowledge and skills in their role of supporting use of interpreters**.**Referral pathways: practice staff will gain an understanding of refugee health referral pathways in the region (including available services, eligibility requirements and referral procedures).

These areas of focus helped the study objectives (see above). All practices recruited will be asked to work on these four core areas as a minimum, with the option to choose an additional 1–2 activities from a list of optional tasks depending on interest and capacity (Table 2).

**Table 2 Tab2:** Intervention Optional activities

Activity	Description
Cultural awareness	Practice staff demonstrate cultural awareness and sensitivity to refugee issues, including an understanding of the refugee experience.
Communication skills	GPs and practice nurses have appropriate communication skills (They are sensitive to the needs of refugees and take time to explain care to patients so they can make informed decisions by understanding what is happening as part of their care).

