### Outcomes

The primary outcomes will be changes in number of claims for the delivery of Medicare Benefits Schedule (MBS) reimbursed comprehensive health assessments among patients identified as being from a refugee background. We will calculate the change in proportion of eligible (within 12 months of arrival in Australia) refugee background patients with medical records where there is evidence of billing for a comprehensive health assessment (MBS items 701, 703, 705 and 707). Secondary outcome measures will be:(i)The change in the proportion of patients with records with recorded refugee identification (country of birth, ethnicity, year of arrival).(ii)The change in proportion of refugee patient consultations with documented use of credentialed interpreter, where one was required.(iii)The change in practice staff knowledge, attitudes and behaviours towards referring refugee background patients to external health and welfare services for which their refugee patients are eligible.

We will also measure changes in general practitioners’ confidence to undertake health assessments, catch-up immunisation and infectious diseases screening, and changes in practice routines relating to health assessments.

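### Secondary outcome (i) can be computed only among patients already flagged as refugee-relevant, so its denominator moves with the intervention and the measured change is selection-biased

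*Protocol article*

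**What the plan says.** The Protocol article, under Outcomes, defines secondary outcome (i) as "The change in the proportion of patients with records with recorded refugee identification (country of birth, ethnicity, year of arrival"). It does not specify the denominator further.

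Under Data collection methods, an add-on report in the CAT4 tool was designed "to allow measurement of general practice performance in key refugee health quality domains including refugee identification, interpreter use and health/mental health assessments". Its searches "will first filter all patient records where identifiers of country of birth, ethnicity or language spoken that are relevant to refugee populations have been recorded". Such an identifier may stand "in a coded field or as free text in the patient record". The result is a line list: "This output will be a de-identified line listed excel spreadsheet that includes (where available) residential postcode, age, gender, country of birth, ethnicity, language spoken, year". The listing runs on to arrival year and further items. On timing, "This data extract will be carried out at baseline and repeated at the end of the intervention period as well as at 6-months post intervention".

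Under Development of the intervention, one of the four core areas asks practices for "accurate and accessible mechanisms in place to record and retrieve refugee identification, status, country of birth or ethnicity, year of arrival, and need for interpreter".

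The only other possible source of a denominator is the Practice Description survey, which "will contain questions regarding a practice’s staffing, patient load and demographics". Table 4 schedules it before the intervention only (twice in late practices). Nothing links it to outcome (i).

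**The concern.** A proportion meant to show whether recording has improved needs a denominator that does not depend on recording. Here a patient enters the file because a refugee-relevant field has been recorded. A refugee-background patient with no such marker is the clearest failure of identification, and that patient is not described as being output at all.

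The intervention tries to increase recording of fields that include the entry fields. A clinic that responds well will therefore bring new patients into its own denominator between extracts. These are repeated cross-sections, so membership of the file is a post-treatment quantity. Randomising practices and fitting the mixed model under Statistical methods do not remove selection of that kind.

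At stake is one of the four core areas of the intervention and a named secondary objective. A clinic that identifies more of its refugee patients could show a gain that is too small, no gain, or a fall.

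**Working it through.** The plan states no rate, target or power for outcome (i), so there is no figure to reproduce. The check compares the fields and then uses assumed figures to show the possible size.

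**Step 1. Fields side by side** (Outcomes against Data collection methods).

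| Field | Admits a record to the extract | Listed in outcome (i) |
|---|---|---|
| Country of birth | yes | yes |
| Ethnicity | yes | yes |
| Language spoken | yes | no |
| Year of arrival | no | yes |

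The two sets overlap but differ. A patient admitted on language alone may lack country of birth and ethnicity, and any listed patient may lack year of arrival. Completeness of each field among flagged patients is therefore calculable, and it is not fixed at 100%. A measure of any entry marker being recorded would be 100% by construction, but the outcome does not list language.

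**Step 2. Country of birth or ethnicity.** Let c be the probability that country of birth or ethnicity is recorded for a true refugee-background patient, and l the same for language. Assume the two are independent and l does not change. Then

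P(recorded | in extract) = c / [1 − (1 − c)(1 − l)].

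Assume 200 true refugee-background patients and c rising from 0.40 to 0.70, a true gain of 30 points.

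| l | Extract size, before → after | In-extract proportion, before → after | Apparent change |
|---|---|---|---|
| 0 | 80 → 140 | 100% → 100% | 0 |
| 0.3 | 116 → 158 | 69.0% → 88.6% | +19.6 points |
| 0.6 | 152 → 176 | 52.6% → 79.5% | +26.9 points |
| 0.9 | 188 → 194 | 42.6% → 72.2% | +29.6 points |

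For example, at l = 0.3 the baseline value is 0.40/(1 − 0.6 × 0.7) = 0.40/0.58 = 0.690. The bias runs from complete masking to almost none, depending on language recording, which the protocol does not report.

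**Step 3. Year of arrival.** Assume 80 of the 200 patients are listed at baseline, 20 of them with year of arrival. Then 60 more enter the extract, a fraction x of them with year of arrival. The in-extract proportion goes from 20/80 = 25.0% to (20 + 60x)/140. The true proportion goes from 20/200 = 10% to (20 + 60x)/200.

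| x | In-extract, after | True, after |
|---|---|---|
| 0 | 14.3% | 10% |
| 0.25 | 25.0% | 17.5% |
| 0.5 | 35.7% | 25% |
| 1 | 57.1% | 40% |

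At x = 0 there is an apparent fall of 10.7 points with no true change. At x = 0.25 a true gain of 7.5 points is invisible. At x = 0.5 a true gain of 15 points shows as 10.7. At x = 1 a true gain of 30 points shows as 32.1.

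**Step 4. A simpler case.** Of 100 flagged patients, 60 have year of arrival: 60/100 = 60%. The clinic flags 50 more by country of birth or language only, so 50% more patients are identified, yet completeness is 60/150 = 40%. If all 50 also have year of arrival, it is 110/150 = 73%.

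**The case against.** The strongest reply is that the outcome is calculable and often moves the right way. Language alone admits a patient, free text is searched, and year of arrival is not an entry field, so each outcome field can be missing among listed patients. In Step 2 every case with some language recording shows a gain, and with high language recording the bias is trivial. The fall to 40% is also a selected case. The intervention targets year of arrival too, and the same example gives a rise to 73% if all new entrants have it. All of this stands, and it limits how much can be claimed.

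A reader might infer that outcome (i) cannot be estimated, that unidentified patients never appear, or that the proportion is near 100% by construction. The documents do not support these readings. The second holds only for patients with no marker at all. The third holds only for a composite of any entry marker.

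A further reply is that this is a condensed article: a statistical analysis plan is promised under Dissemination policy, a separate cleaning protocol is mentioned under Data management, and the article does not say that the report gives no practice totals. The exact denominator could indeed be defined elsewhere. But the article does fix the filter and the output, and no later analysis of a filtered line list can recover patients or totals that were never extracted. This part of the reply therefore does not dispose of the point.

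**Conclusion.** The concern holds in a limited form. As described, outcome (i) is conditional on a refugee-relevant country of birth, ethnicity or language already being recorded. It leaves out patients with no marker, and its denominator changes with treatment. The change in field completeness is therefore selection-biased. Under the assumed figures, a true gain of 30 points in country-of-birth or ethnicity recording appears as anything from 0 to +29.6 points. Year-of-arrival completeness can fall, stay level or rise, depending on how many newly flagged patients have it recorded.

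These sizes rest on assumed counts and recording rates, on independence of the fields, and on language recording staying constant. The direction of the argument needs only the stated filter and the stated aim of the intervention.

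A reader might also infer that the other core outcomes fall with this one, or that the primary comparison is undermined. Neither is shown here. Outcome (iii), for example, concerns staff knowledge, attitudes and behaviours rather than the filtered records. This is a secondary outcome, so the change should be made but is not a condition for the trial to proceed.

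**What to change.** At every CAT4 extract, also output per-practice aggregate counts of all active patients and of those with country of birth, ethnicity and language completed. State the rule for an active patient and keep it the same at all time points. Then:

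- define outcome (i) for country of birth and for ethnicity as completed records over all active patients;
- analyse refugee-flagged patients per 1,000 active patients beside it, since this is the quantity that rises when a clinic identifies more refugees;
- report year-of-arrival completeness only among flagged patients, labelled as conditional on being flagged. Taken over all active patients it would not be sensible, because it does not apply to those born in Australia.

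The cost is a small addition to the extract report, with no added patient-level data. Whether the tool can produce the counts, and whether existing approvals cover them, should be confirmed, because the documents do not say. The new measure also partly reflects general demographic recording rather than refugee identification alone, which is why the flagged-patient rate is needed with it. For any extract already taken without these counts, the line list cannot supply them, and results from that time point should be described as conditional.

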
### Data management

Survey data will be collected using electronic or paper based forms. All survey data will be entered into Qualtrics then checked for accuracy and completeness prior to de-identification. Patient data will be extracted from practice records using PENCS CAT4 in de-identified format. Trained researchers will clean quantitative data using a protocol created in collaboration with the project biostatistician. Quantitative data will be exported to SPSS or Stata for analysis.

Audio files of interviews with practice staff will be de-identified and transcribed verbatim. Interview transcripts, facilitator diaries and other documents will be exported to NVivo for analysis.

### Statistical methods

Changes in practice performance relating to the primary outcome measure will be assessed between early and late intervention practice groups using multilevel mixed effects models to account for clustering as recommended for stepped-wedge cRCT designs [19, 20]. All quantitative outcome measures will be assessed for clustering, and if not significant may be further explored through uni-level multivariate methods (e.g. logistic regression to investigate factors affecting the proportion of consultations with interpreter use). However, if practice-level clustering is indicated, then the mixed models will include a cluster-specific random effect to deal with clustering at the practice level. In the main analysis the independent variables defined as fixed effects will be group allocation (1 = early, 0 = late), intervention status (0 = pre-intervention, 1 = post-intervention) and timepoint (0 = baseline for all practices, 1 = post intervention for early practices, pre-intervention for late start practices, 2 = 6 months post intervention for early practices, post intervention for late start practices, 3 = 6 months post intervention for late practices). Timepoint will be included as a categorical variable. In subsequent analyses, provider and practice level covariates thought to influence outcomes will be included to adjust for baseline differences between the two groups.

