**Methods:**

Our mixed methods study will use a cluster stepped wedge randomised controlled trial design set in 3 urban regions of high refugee resettlement in Australia.

The intervention was build upon regional partnerships of policy advisors, clinicians, academics and health service managers. Following a regional needs assessment, the partnerships reached consensus on four core areas for intervention in general practice (GP): recording of refugee status; using interpreters; conducting comprehensive health assessments; and referring to refugee specialised services.

Refugee health staff trained in outreach practice facilitation techniques will work with GP clinics to modify practice routines relating to the four core areas.

36 general practice clinics with no prior involvement in a refugee health focused practice facilitation will be randomly allocated into early and late intervention groups.

The primary outcome will be changes in number of claims for Medical Benefit Service reimbursed comprehensive health assessments among patients identified as being from a refugee background. Changes in practice performance for this and 3 secondary outcomes will be evaluated using multilevel mixed effects models.

Baseline data collection will comprise (i) pre-intervention provider survey; (ii) two surveys documenting each practices’ structure and approaches to delivery of care to refugees. De-identified medical record data will be collected at baseline, at the end of the intervention and 6 and 12 months following completion.

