### Objectives

Our overall objective is to conduct a mixed methods evaluation of a practice facilitation intervention designed to improve the primary care management of refugees in 36 general practice clinics across 3 regions: South East Melbourne (SEM), North West Melbourne (NWM) and South West Sydney (SWS).

We asked whether a facilitation-based intervention directed at improving the quality of general practice-based primary care delivered to patients with a refugee background could increase:The conduct and documentation of comprehensive physical and mental health assessments among patients identified as being from a refugee background (primary outcome)

Secondary outcomes:2.Refugee status determination and recording3.The use of credentialed interpreters among patients identified as being from a refugee-like background4.Practice staff knowledge and use of referral pathways to refugee specific health and social welfare services

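### The practice random effect depends on a significance check for clustering, although practices are randomised; the harm falls mainly on practice-level analyses with few records, and the primary effect estimate is not shown to be affected.

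*Protocol article*

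**What the plan says.** The Statistical methods section opens by assigning the primary outcome to analysis "using multilevel mixed effects models to account for clustering as recommended for stepped-wedge cRCT designs". The next sentence covers every quantitative outcome: "All quantitative outcome measures will be assessed for clustering, and if not significant may be further explored through uni-level multivariate methods". Its example is a logistic regression of factors related to interpreter use. The sentence after that reads: "if practice-level clustering is indicated, then the mixed models will include a cluster-specific random effect to deal with clustering at the practice level". The main-analysis specification follows directly: "In the main analysis the independent variables defined as fixed effects will be group allocation (1 = early, 0 = late), intervention status" and categorical timepoint.

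The Abstract carries no such condition: "Changes in practice performance for this and 3 secondary outcomes will be evaluated using multilevel mixed effects models".

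Under Allocation, the unit is the practice: "practices will undergo blinded, stratified random allocation into either an early or late intervention group". The Objectives set the study "in 36 general practice clinics across 3 regions". The Sample size section plans on an ICC of 0.05 with 30 patients per clinic at each timepoint. The article names no test for clustering and no significance level for it.

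**The concern.** When practices are allocated, records from one practice share that allocation and that practice's habits. The analysis should respect this whatever a test reports. A non-significant test does not show independence, and with few records per practice it has little power to find clustering of the size that the plan itself expects. A mixed model from which the practice effect has been dropped is a single-level model. The rule therefore conflicts with the Abstract and with the section's own first sentence. It also lets the model be chosen after the data are seen, with no stated criterion.

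If the single-level route is taken while clustering exists, standard errors are too small for anything that varies between practices: practice size, region, staffing, and the planned practice-level covariates.

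**Working it through.** **The plan's own figures.** The article gives no error rate for this rule, so there is none to reproduce. Its sample size does rely on clustering: the design effect is 1 + (30 − 1) × 0.05 = 2.45. The baseline proportion is not stated. With an assumed 37.5% against 62.5%, 62 per arm × 2.45 / 30 = 5.06, so 6 clinics per arm, or 12, which agrees with the stated number.

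**Inputs.** From the documents: 36 practices, ICC 0.05, 30 records per timepoint, and three data collections in early practices and four in late ones. Assumed: ICC 0.02 as a lower value, 3 or 5 records per practice per timepoint, a 5% clustering test, and a two-sided 5% test of the factor. Small counts are plausible because the practitioner survey goes to each consenting GP, practices are stratified at 5 full-time-equivalent GPs, and the primary denominator is limited to patients within 12 months of arrival. The article gives no actual counts.

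**Formulas.** Let n be records per practice summed over timepoints, with practice effects constant over time.

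- Design effect: DE = 1 + (n − 1) × ICC.
- Error for a null practice-level factor if clustering is ignored: 2 × [1 − Φ(1.96/√DE)].
- Chance that the test misses clustering (one-way F test): P(F < Fcrit / (1 + n × ICC/(1 − ICC))), with 35 and 36(n − 1) degrees of freedom.

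| ICC | records × timepoints = n | DE | Error if ignored | Test misses |
|---|---|---|---|---|
| 0.05 | 30 × 1 = 30 | 2.45 | 21.0% | 1.7% |
| 0.05 | 5 × 1 = 5 | 1.20 | 7.4% | 76.4% |
| 0.05 | 5 × 4 = 20 | 1.95 | 16.0% | 9.8% |
| 0.05 | 3 × 1 = 3 | 1.10 | 6.2% | 87.0% |
| 0.05 | 3 × 4 = 12 | 1.55 | 11.5% | 35.0% |
| 0.02 | 5 × 1 = 5 | 1.08 | 5.9% | 89.5% |
| 0.02 | 5 × 4 = 20 | 1.38 | 9.5% | 56.6% |
| 0.02 | 3 × 1 = 3 | 1.04 | 5.5% | 92.4% |
| 0.02 | 3 × 4 = 12 | 1.22 | 7.6% | 75.9% |

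At ICC 0.05 with 30 records, pooling two or more timepoints brings the miss rate to 0.0%.

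**Simulation of the rule itself.** With a likelihood-ratio test of the random intercept over the plan's timepoints and 36 practices:

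- The test misses clustering at ICC 0.05 in 19% (5 records) and 46% (3 records) of trials. At ICC 0.02 it misses in 66% and 81%.
- Given a miss, a null practice-level factor is significant in 15.4% (ICC 0.05, 5 records), 11.0% (0.05, 3), 10.6% (0.02, 5) and 8.4% (0.02, 3) of trials.
- With one or two timepoints the conditional rate falls to about 6% to 10%.
- Counting all trials, whether or not the test misses, the rule's error is about 5% to 7%, against about 5% when the practice effect is always kept.

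**The intervention coefficient.** In the main model (group, timepoint, intervention status) with no random effect, the intervention term rejects a true null in about 4% to 6% of trials when practice effects are constant over time, because a constant effect cancels. With an assumed autocorrelation of 0.5 between timepoints it reaches about 15% at ICC 0.05. At that ICC, with 36 practices and 30 records, the pooled test missed clustering in 0% of simulated trials, so the rule would not drop the effect there.

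**The case against.** The strongest defence is that the single-level route is permissive and exploratory. The primary outcome is first assigned to mixed models, the wording is that outcomes may be explored further, and the only example is a secondary analysis of interpreter use. This is a fair reading of that sentence. It does not cover the next one, which ties the random effect in the mixed models generally to an indication of clustering and stands directly before the main-analysis specification. At best the text is ambiguous. Even on the narrow reading, the exploratory analyses are the ones exposed.

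The second defence is that at the planned size the test almost always finds clustering. That stands, and it limits the point.

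Two stronger readings are tempting and are not supported.

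- A reader might infer that the trial would give falsely significant practice-level results as often as 21% of the time. At ICC 0.05 and one cross-section of 30 records, 21.0% is the error if clustering is ignored, but the rule reaches that branch in under 2% of trials with 36 practices. In the small-record simulations 21% appears only at ICC 0.10 with 3 records, and neither value is in the documents. These are conditional rates and not the trial's error rate.
- A reader might infer that the intervention effect is biased or its test invalid. That is not shown when practice effects are stable. The inflated figure of about 15% needs both an autocorrelation that the documents do not give and a dropped random effect in a setting where the test would keep it.

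**Conclusion.** The point holds as a defect in the stated rule, with modest numerical consequences. A practice-randomised trial should not make its practice effect conditional on a test, and the Statistical methods text conflicts with the Abstract.

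At the plan's own inputs the test misses clustering in 0% to 2% of trials, and the primary effect estimate is not shown to be affected. The exposure lies in secondary, survey and practice-level factor analyses with few records. There, under the assumed 3 to 5 records, ICC 0.02 to 0.05 and 1 to 4 timepoints, clustering is missed in about 10% to 93% of trials. Given a miss, the error for a null practice-level factor is about 6% to 15%. Overall the rule costs up to about 2 percentage points (about 5% to 7% against about 5%). Of these inputs only the ICC of 0.05 and the timepoints come from the documents, and the intervention result assumes practice effects that are constant over time.

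**What to change.** In Statistical methods, delete the sentences that make the practice random effect depend on a check for clustering and that allow single-level models when the check is not significant. Replace them with a statement that every quantitative model, main or exploratory, includes practice as a random effect regardless of its estimated size or significance, and that the ICC is reported with its interval for each outcome. This brings the section into line with the Abstract and the sample size.

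The cost is wording only: no extra data or practices are needed. If the practice variance is estimated as zero, the mixed model returns the single-level result anyway.
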